## Abstract

**Background:**

Optimizing pain care requires ready access and use of best evidence within and across different disciplines and settings. The purpose of this randomized trial is to determine whether a technology-based “push” of new, high-quality pain research to physicians, nurses, and rehabilitation and psychology professionals results in better knowledge and clinical decision making around pain, when offered in addition to traditional “pull” evidence technology. A secondary objective is to identify disciplinary variations in response to evidence and differences in the patterns of accessing research evidence.

**Methods:**

Physicians, nurses, occupational/physical therapists, and psychologists (n = 670) will be randomly allocated in a crossover design to receive a pain evidence resource in one of two different ways. Evidence is extracted from medical, nursing, psychology, and rehabilitation journals; appraised for quality/relevance; and sent out (PUSHed) to clinicians by email alerts or available for searches of the accumulated database (PULL). Participants are allocated to either PULL or PUSH + PULL in a randomized crossover design. The PULL intervention has a similar interface but does not send alerts; clinicians can only go to the site and enter search terms to retrieve evidence from the cumulative and continuously updated online database. Upon entry to the trial, there is three months of access to PULL, then random allocation. After six months, crossover takes place. The study ends with a final three months of access to PUSH + PULL. The primary outcomes are uptake and application of evidence. Uptake will be determined by embedded tracking of what research is accessed during use of the intervention. A random subset of 30 participants/ discipline will undergo chart-stimulated recall to assess the nature and depth of evidence utilization in actual case management at baseline and 9 months. A different random subset of 30 participants/ discipline will be tested for their skills in accessing evidence using a standardized simulation test (final 3 months). Secondary outcomes include usage and self-reported evidence-based practice attitudes and behaviors measured at baseline, 3, 9, 15 and 18 months.

**Discussion:**

The trial will inform our understanding of information preferences and behaviors across disciplines/practice settings. If this intervention is effective, sustained support will be sought from professional/health system initiatives with an interest in optimizing pain management.

**Trial registration:**

Registered as NCT01348802 on clinicaltrials.gov.

## Background

Acute and chronic pain affects a large number of Canadians. The prevalence of chronic pain in Canadian adults has been estimated to range from 18–29% [1-4], with 60% experiencing major losses of occupation or function [5]. The 2005 Canadian Community Health Survey found that chronic pain affected 27% of community seniors [2]. In Canada, current healthcare spending to address this problem is $6 billion/year [5] and, with an aging population, is expected to rise to $10 billion/year by 2025.

There is considerable variation in practice and widespread patient dissatisfaction with the way pain is managed across the spectrum, from relatively benign conditions to terminal illness. For example, in low back pain [6], unresolved pain is a common reason for repeat visits. Inadequately managed pain in serious illness is the most common reason for requesting assisted suicide [7]. Conversely, there are societal concerns about the use of narcotic medications for pain management and the potential societal impacts of misuse [8].

Many clinicians are not aware of recent pain research, and misconceptions are common [9,10]. In fact, health professionals may begin clinical practice with insufficient knowledge about pain, as illustrated by an entry-level curriculum for physicians, nurses, and rehab professionals. The majority (68%) of programs did not specify designated hours for pain education (only 32.5% of the respondents could identify specific hours allotted for pain course content), and the total amount of time allocated to pain varied from 13 to 41 hours. Of interest, veterinarians spent twice as much time studying pain [11]. Studies that cross different types of pain and health professions indicate a large gap between evidence and practice—this is reflected by a high prevalence of low competence/confidence in pain management [12-19].

Pain management is central to health disciplines. Physicians, nurses, and rehabilitation professionals are commonly involved in managing acute and chronic pain [20]. Pain is one of the most common reasons for patients to consult these professions [21]. While scope of practice and focus may vary across professions, pain management provides an important context to study professional differences in use of evidence since pain is a high priority to all and an area where interprofessional practice is supported by evidence [22-26].

Evidence-based practice (EBP) can narrow the gap between research knowledge and practice [27]. Studies suggest that an EBP approach is used in nursing [28], medical [29], and rehabilitation practice [30-32] with variable success. Increased use of evidence-based approaches [33] or supports such as guidelines or decision aids is linked to improved clinical decision making and patient care [34,35], but the effects are not consistent [36,37] and, thus, cannot be assumed to work in all contexts.

Professional associations and individual clinicians in rehabilitation are highly supportive of EBP [30,32,38-45]. Despite positive attitudes and motivations about EBP, many studies have reported barriers to effective implementation of evidence from research in clinical practice [46]. Several studies indicate that clinicians experience time as an obstacle to searching for research evidence [47,48]. Clinicians also admit that they lack the skills required to navigate literature databases and to appraise medical literature effectively [32,49,50]. A lack of time [40-42] combined with inadequate searching and appraisal skills [20,21,43-45] are the primary barriers reported. It has been determined that it requires 53 minutes on average—divided between database searches (39 minutes) and obtaining the articles (25 minutes)—to answer a clinical question using a traditional EBP approach [51].

Traditional approaches to knowledge translation (KT) in EBP have focused on providing knowledge and technical EBP “skills” to practitioners, leaving them with the burden of searching and appraising evidence [40,52-56]. Studies suggest these interventions change knowledge about EBP, but not behavior [57,58]. Practitioners have limited success “pulling out” relevant quality evidence because they lack the required searching, filtering, and appraisal skills [40-43,51,54,59,60]. Even with training, the time demands are substantial [51,56]. Current tools provide primitive alerting services that do not target specific practitioners, but send information by “dumping” procedures. As a result, practitioners are overwhelmed with a large volume of information, most of which does not pertain to their practice area. Thus, either these services are not used or alerts are ignored. A basic flaw in both the training or dumping-out KT approaches is that they fail to resolve the essential barriers of time pressures and lack of appraisal/filtering skills.

Evidence-based decision making originated within medicine and evolved to other professions. Limited studies, mostly in the United Kingdom, have addressed differences in attitude or awareness across professions [61,62]. Familiarity with evidence resources is less than might be expected. In 2009, only 44% of urologists were unaware of the PubMed search engine, and only 14% used it regularly [63].

Systematic reviews suggest technology-based EBP can enhance care [34,64,65], although evidence is sporadic. Working directly with the Health Information Research Unit (HIRU) at McMaster University, we developed an approach to push out targeted, clinically relevant, high-quality research evidence to practitioners. This Premium LiteratUre Service (PLUS) [66,67] removes the burden of appraising research evidence, as technical experts perform basic critical appraisal, and then filters the high-quality studies and systematic reviews with ratings of relevance and interest from expert clinicians from the field to send only what is clinically relevant and new to the individual clinician. We know this approach increases uptake in physicians [66] and is valued by nurses [28] and rehabilitation users (pilot data). In a cluster randomized trial funded by the Canadian Institutes of Health Research, with physicians in Northern Ontario, PLUS was shown to increase the use of medical literature by 57% and substantially increase the depth of use of evidence-based resources [57]. One of the limitations in KT research on this topic to date has been the use of surrogate outcome measures of knowledge utilization. It can be challenging to measure how new knowledge is integrated into clinical decision making, particularly in areas where complex reasoning is required. This study is designed to address some of those deficiencies.

The primary objective of this randomized crossover trial is to evaluate the incremental effect of a PUSH evidence resource (Pain PLUS) across professions (physicians, nursing, rehabilitation, psychologists) as compared to a standard (PULL) approach. The primary outcomes are uptake and application of evidence, and they will be assessed at baseline, 3, 9, 15 and 18 months.

## Methods/design

The trial is a crossover randomized controlled trial (RCT) with repeated baseline and follow-up measurements (Figure 1). The interventions are two different types of access to pain research evidence for four different types of professionals involved in pain management. The trial will begin with a three-month (repeated) baseline, during which average participant use of the standard PULL resource will be monitored. Participants will then be randomly allocated to either receive PUSH + PULL or continue to use the PULL resource. After six months, participants will cross over to the alternate intervention for an additional six months. To complete the trial, both groups will finish with three months of PUSH + PULL access. The repeated baseline period provides more stable estimates of participants’ access prior to randomization. The rationale for the crossover design is that it will maximize our statistical efficiency, increasing the precision of effect estimates. This is particularly important for our subgroup (profession) estimates; it will also provide better control of unknown potential confounders. The main potential drawback of a crossover design occurs if the “wash-out” is incomplete. While we will have control of the intervention delivery, the exposure to email alerts may affect use of the pull resources; therefore, we will test for order effects. The study received Ethics Approval from the McMaster University Research Ethics Board.

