#### Mediators of use of evidence/intervention response

It is important to monitor and potentially adjust for important covariates that influence study outcomes. We will measure the following variables for each clinician: baseline knowledge/attitudes towards EBP, years of practice, highest degree, and comfort with technology. Organizational variables will also be collected at baseline, including rural/urban location, clinic size, access to online journals, peer support, administrative support, and management support. These variables will be entered into an analysis of covariance examining pre- and post-intervention effects. Our sample size is sufficiently large that we will be able to assess the primary effects of these variables, as well as interactions between organizational variables and participant variables.

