#### Sample-size calculations

To determine the appropriate sample size for this trial, the following factors were considered: (1) the primary and secondary outcomes in the trial, (2) clinically significant differences for the outcomes based on our previous RCT, (3) Type I (alpha) and Type II (beta) errors, (4) estimates of variation from our pilot data, (5) study design, and (6) dropouts. These calculations represent sample size for the overall comparisons between the four professional groups and two intervention groups. Sample-size estimation was based on detecting an effect size of 0.40 between groups on any of the three aspects of outcome (usability, usefulness, and knowledge/attitude/behavior). Assuming Type I error = 0.05 (two-tailed), Type II error = 0.80, and the effect size = 0.40, the sample size required per group is 80. The sample size required for two comparison groups across four professions = 80 × 2 × 4 = 640. To account for our dropout rate (8/431), we have conservatively added 30 to recruit a sample of 670 practitioners. For analysis of response mediators, an *R*^2^ of 30% corresponds to an effect size of 0.42; 600 practitioners provides more than 99% power to detect this effect size with 12 predictors [79].

This study is organized locally but recruits participants internationally to inform practitioners of the study and the potential for free access to evidence resources. Our multimodal recruitment strategy will use professional associations, websites/conferences, and social media to inform practitioners of the study and the potential for free access to evidence resources.

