#### Planned data analyses

Quality checking of primary and secondary outcome data will be performed by re-entry of 100 cases and checking concordance. Descriptive statistics, including frequencies, means, and standard deviations, will be calculated and data displayed graphically for all study variables as a means of exploring data distributions. The data for all outcome measures will be analyzed to ensure that they meet the statistical assumptions necessary to use parametric statistics. Transformations may be considered if necessary to meet test assumptions. To test our main research question, we will use general, linear mixed-effects models [82] for repeated measurements over time to explore the relationship among the use/behavior scores, comparing the effects between professional groups and intervention types. The models will be fitted for the outcome scores over time as a function of the between-participant (profession/intervention) and within-participant (time) variables. Utilizing a mixed-model approach allows us to account for the dependence between outcome measurements taken over time from the same participant. The structure of the variance-covariance matrix, which dictates the dependence between measurements in the fitting of the model, will be chosen based on standard criteria in statistics. *Post hoc* pairwise comparisons of the two treatment arms at different time points will be done using multiple comparisons with adjustment to the Type I error rate. Type I error will be set to 5% (*i.e.*, α = 0.05) for all the calculation of the confidence intervals and performing the various hypothesis-testing procedures. Type I error will be adjusted accordingly for multiple comparisons. Standard diagnostic tools will be used to assess any of the model fittings. An intent-to-treat analysis will be employed—those who do not participate will be included in the analysis in their original group. No interim analyses are planned since there are no safety issues and we wish to ensure full power for both primary and secondary analyses.

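### Run-in usage, the baseline KABQ Behaviour score and baseline chart-stimulated recall are collected but not named as covariates for their own outcomes, which costs precision in the plan's between-person comparisons

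*Protocol article*

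**What the plan says.** Methods/design describes three months of monitored PULL use before allocation and gives the reason: "The repeated baseline period provides more stable estimates of" participants' access before randomisation. Randomization places allocation at month 3 and crossover at month 9. Timing of measures has the KABQ at 0, 3, 9, 15 and 18 months, so two KABQ scores precede the randomised periods. CSR is done in 30 per group, at baseline and nine months only.

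Planned data analyses fits a mixed model to the outcome scores over time "as a function of the between-participant (profession/intervention) and within-participant (time) variables", followed by post hoc "pairwise comparisons of the two treatment arms at different time points". No baseline term is named.

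The section on mediators lists clinician covariates, "baseline knowledge/attitudes towards EBP, years of practice, highest degree, and comfort with technology", together with organisational variables, and enters them in an analysis of covariance. Run-in usage, the KABQ Behaviour score and CSR are not on that list.

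Sample-size calculations treats the trial as parallel groups within profession: "Sample-size estimation was based on detecting an effect size of 0.40 between groups", and "the sample size required per group is 80". It takes no credit for the crossover or for baseline data.

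**The concern.** The run-in is collected for precision, and uptake and application of evidence are the stated primary outcomes. Yet the pre-randomisation values of usage, self-reported EBP behaviour and CSR have no stated place in the model that estimates the treatment effect on them.

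In a pure within-person contrast this would hardly matter, because each participant serves as their own control. But several of the plan's comparisons are between persons:

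- The model lists intervention as a between-participant factor, and the arms are compared at separate time points.
- CSR is measured only in the first period, so its treatment comparison cannot be within-person.
- Methods/design accepts that alerts may alter later PULL use and plans a test for order effects. If that test is positive, the analysis falls back on the first period or on a carryover-adjusted estimate.

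In all three, stable differences between people stay in the error term unless the baseline is used. Chance imbalance between the arms within a profession also goes uncorrected.

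**Working it through.** **Inputs from Sample-size calculations.** Effect size 0.40 (SD = 1), two-sided alpha 0.05, 80 per group in each profession. The printed "Type II error = 0.80" is read as 80% power. The baseline-to-follow-up correlation r is not given, so a range is assumed.

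**1. The plan's own figure.** n per group = 2(1.960 + 0.842)² / 0.40² = 98.1, so 99 (99.1 by the t-test). The stated 80 is not reproduced two-sided; a one-sided test gives 78. With 80 v 80, two-sided t-test power is 71.0% (normal approximation 71.6%).

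**2. Adding the participant's own baseline.** One baseline multiplies the residual variance by 1 − r², so the effective effect size is 0.40/√(1 − r²). The mean of two baselines, with equal correlations r throughout, multiplies it by 1 − 2r²/(1 + r). Example at r = 0.5: one baseline gives 0.40/√0.75 = 0.462; the mean of two gives 0.40/√(1 − 0.333) = 0.490.

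| Assumed r | One baseline | Mean of two |
|---|---|---|
| 0 | 71.0% | 71.0% |
| 0.3 | 75.0% | 77.3% |
| 0.4 | 78.3% | 81.7% |
| 0.5 | 82.7% | 86.9% |
| 0.6 | 88.2% | 92.4% |

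(80 v 80, two-sided t-test; the normal approximation is up to about half a point higher.) Power of 80% needs r of about 0.43 to 0.45 with one baseline and about 0.35 with the mean of two.

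**3. Does including the early scores as repeated outcomes already give this gain?** Generalised least squares, 80 per arm, compound symmetry, complete data, months 0, 3 and 9 as outcomes, assumed r = 0.5:

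- Free arm-by-time means: the variance of the month-9 arm difference is 0.0250 = 2/80, the same as with no baseline.
- Arm means held equal at months 0 and 3: variance 0.0250 × (1 − 0.333) = 0.0167.

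The gain depends on the constraint (or the covariate), and the article states neither.

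**4. The crossover contrast.** Per profession, 80 per sequence, r = 0.5, normal approximation:

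| Model | Without pre-randomisation scores | With both |
|---|---|---|
| No carryover term | 99.9% | 99.9% |
| Carryover term | 71.6% | 87.3% |

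Without carryover, power is already 94.7% at r = 0, and the baselines add nothing under compound symmetry. A carryover term takes the precision back to that of the first period alone (variance 0.0250), and the baselines then matter again.

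**5. CSR.** 30 × 4 = 120 participants, about 60 v 60 pooled over professions if split evenly. Carrying over the effect size of 0.40 (the article states none for CSR), power is 58% unadjusted and 71% with baseline CSR at an assumed r = 0.5.

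**The case against.** The case on the other side has real substance.

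- **Some baseline adjustment is planned.** The mediators section puts baseline EBP knowledge/attitudes into an analysis of covariance of pre- and post-intervention effects. This stands: a reader might infer that the plan makes no baseline adjustment at all, and the document does not support that. The gap is limited to run-in usage, KABQ Behaviour and CSR, and to the mixed model that answers the main question.
- **The mixed model may take months 0 and 3 as outcomes.** It may, since the article says outcomes are assessed at those times. If intervention is coded as received, both arms are on PULL until month 3 and share a mean, which would deliver the gain. But the text lists intervention as between-participant and compares arms by time point; with free arm-by-time means the gain is nil (step 3). The article does not settle which applies.
- **The main contrast has ample power.** This stands if there is no carryover. The parallel comparison pooled over professions, 320 v 320, also has 99.9%. The 71% concerns between-arm comparisons within one profession, and the time-point comparisons are labelled post hoc.
- **Covariate choice belongs to an analysis plan that is not shown.** That lowers the weight of the point. However, the article itself states the model terms and the covariate list, and these leave out the data it says the run-in was designed to supply.
- **CSR is described as before and after.** Its baseline will be reported, but no model using it as a covariate is stated.

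A reader might also infer that adjustment would restore the stated 80% power. That depends on a correlation the article does not give: at r = 0.3 one baseline reaches only 75%.

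**Conclusion.** The point holds as a missed gain in precision, confined to between-person comparisons. Run-in usage, baseline KABQ Behaviour and baseline CSR have no stated role as covariates for their own outcomes. For a within-profession comparison of 80 v 80 at effect size 0.40, using one baseline would raise power from about 71% to between 78% and 88% for correlations of 0.4 to 0.6. If a carryover term is needed, using both pre-randomisation scores would raise it from 71.6% to 87.3% at r = 0.5.

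These figures assume equal correlations over time, complete data and outcomes reasonably close to normal; every value of r is an assumption. The within-person contrast without carryover is unaffected. The shortfall against 80% power arises from the sample-size arithmetic (80 v 99 per group), not from the missing covariates, and it remains an error whichever model is used.

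**What to change.** In Planned data analyses, state that the treatment-effect model for each outcome includes the participant's own pre-randomisation value. It can enter either as a covariate, with only post-randomisation measurements as outcomes, or as a repeated outcome with the arm means constrained equal before randomisation. The values are:

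- usage: run-in accesses per month, on a scale that allows zeros, such as log(x + 1), because the Compliance section keeps non-users in the analysis and a plain log is undefined for them;
- KABQ: the mean of the 0- and 3-month scores on the same subscale;
- CSR: the baseline score.

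Say how this relates to the analysis of covariance in the mediators section. Keep the comparison of professions at baseline, planned under the secondary objective, as a separate analysis, since it needs the baseline values as outcomes.

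The cost is a few sentences and no new data collection. The sample-size statement needs its own correction.
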